### 2.3.3. Rationale for intervention's "dose," frequency, and administration:

Weekly PQ-Surveys: Surveys will be administered weekly to capture distress in real time. A longer interval may make the intervention less relevant if surveys miss the distress event or participants answer about distress that occurred longer ago. Ideally, one would want participants to report distress on an "as needed" basis, however this approach is challenging from a design point of view as controls may have less incentive to report. For this reason, we decided to collect weekly measures in both arms. Weekly reporting allows the Response team to intervene and propose prevention strategies if symptoms are thought to be recurrent. During the pilot, adherence to weekly surveys was good; over 75% of participants answered 50% of weekly surveys or more, and 60% answered 75% of weekly surveys or more.

Response team intervention: Response teams will contact the families: (i) on a regular basis over the intervention period (we encourage at least monthly encounters), (ii) to attend to PQ reports, and (iii) to monitor treatment recommendations. Regular contacts are proposed as a means of standardizing the intervention across patients with varying experiences of distress.

Response teams will be informed of criteria for potential distress including:

- a. a PQ-MSAS total score of 3.2 or higher (for children using PQ-MSAS 7-12 (see section 2.5.1.) the equivalent threshold value is 9) or individual symptom scores of 50 or more, or
- b. PedsQL total score below 60.

A PQ-MSAS score of 3.2 (or 9) was chosen as a threshold because it is the minimum score that includes one severe symptom (i.e. that participant reported at least two of the following characteristics for a given symptom: it is very severe, or happens almost all the time, or bothers him/her a lot or very much). It could also represent a report with five mild or moderate symptoms, which also warrants evaluation. In addition, teams will be advised that any symptom score of 50 or more may indicate current or past distress. Similarly, the score of PedsQL of 60 denotes a poor quality of life (this represents approximately one standard deviation below the average PedsQL score in pediatric cancer populations). These threshold scores will promote optimal Response team intervention. Further, this approach helps standardize the response to distress and as such increases replicability of the intervention.

## 2.4. Outcomes

### 2.4.1. Primary Outcome Measures (aim 1)

Child Quality of Life: Difference between the two treatment arms in the mean over 16-weeks (16-w) of PedsQL total score as reported by (a) the parent for all enrolled patients, and (b) the patient if 5 years of age or older. PedsQL scores range from 0-100 (higher better) and are calculated as the average of all 22 items (total score). For each weekly administration, scores are calculated if >50% of the PedsQL items are answered. Treatment success will be defined as a difference of at least the minimal clinically important difference (MCID) between groups. The MCID for PedsQL total score is 4.4 points.

## 2.4.2. Secondary Outcome Measures

### 2.4.2.1. Patient-level outcomes (aim 1)

**Child Quality of Life:** Difference between the two treatment arms in the mean over 16-weeks (16-w) of PedsQL sub-scale scores (physical and psychosocial) as reported by (a) the parent for all enrolled patients, and (b) the patient if 5 years of age or older. PedsQL subscale scores are calculated as the average of 7 physical items and 15 psychosocial items respectively. The same scoring ranges and rules as explained for total score apply. MCID for PedsQL for the physical and psychosocial subscale scores is 6.7 and 5.3 points respectively.

**Symptom burden scores:** Difference between the two treatment arms in the mean over 16-w of PQ-MSAS total and sub-scale scores (PHYS and PSYCH sub-scales) as reported by (a) the parent of all enrolled patients and (b) the patient when 13 years old or older. PQ-MSAS scores range from 0-100 (lower better) and are calculated as the average of all 26 individual symptom scores (total score), 8 physical and 6 psychological items for the sub-scale scores. Individual symptom scores are derived as the average of each symptom's reported frequency, severity and extent of bother scores. For each weekly administration, PQ-MSAS scores are calculated if >50% of the symptoms are answered. As mentioned in 1.3.2, PQ-MSAS has an age-adapted instrument from the age of 7 (PQ-MSAS 7-12). However, as compared to the PQ-MSAS 13-18 (self-report for teens) and the parent versions, PQ-MSAS 7-12 is much shorter (only asks about 8 symptoms) and uses a different response scale. The data on PQ-MSAS 7-12 will be collected and used for feedback reports but not for hypothesis driven outcome analysis; for this age group, only parent reported symptom burden will be analyzed. Child-reported data will be used to conduct exploratory analysis.

### 2.4.2.2. Parent-level outcomes (aims 2 and 3)

**Parent Psychological Distress:** Difference between the two treatment arms in the mean over 16-w of anxiety and depression scores measured on a monthly basis by S-TAI-State and CES-D-10; and on symptom-related stress measured at study entry and at week 16 by *a*RSQ-Stress. Scoring details are presented in section 2.5.1.

**Family activation:** Difference between the two treatment arms in (a) Change in active coping, planning, and instrumental support Brief-COPE scale scores between week 16 and baseline, ordinal variables; (b) Total No. and (c) No. of different complementary therapies used for symptom treatment (reported by parents every 4 weeks), and (d) use of psychosocial services, as measured by total No. of psychosocial clinician encounters documented in the medical record, over the 16-w study period.

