## 2.5. Participant timeline

Participants' timeline is presented in Figure 8. Study participants will be assessed using the PediQUEST web system. At all sites, immediately following consent, the RC will help families register in the system and download the mobile App. All participating parents will be provided with a PQ account, linked to an email of choice. In the case of children aged 2 to 4 years old, only parents will answer PediQUEST Surveys. In the case of children aged 5 to 7 years old, parents and children answer PediQUEST Surveys which are sent to the parent's account; it is expected that parents read the questions out loud to the child. Patients  $\geq 8$  years old will be provided with a PQ account of their own (will need a different email than the one provided by their parent) and will answer PQ-Surveys on their own; in addition, their parents will answer proxy versions (see section 2.5.1). Once a PQ-Survey is assigned, a link is sent by email/notification to the corresponding PQ account owner. In addition, questionnaires can be handed over to participants using the research team tablet for completion, or answered over the phone (administered by the RC) if the participant prefers. PQ Reports will only be available for participants assigned to the intervention arm during the 16 weeks after randomization. After registration, the RC will manually assign the Baseline Packet (30 minutes, online parental survey, preferably answered at the clinic or ward at the time of enrollment). Over a total of 18 weeks (2-week run-in period and 16-weeks post-randomization follow-up), parents and patients  $\geq 5$  years old in both arms will be automatically assigned weekly PediQUEST surveys (10 minutes each, online self-administered surveys answered from any location, provided there is access to internet connection). In addition, parents of both arms will be assigned Monthly Parent Questionnaires evaluating distress, burden, and use of complementary therapies every 4 weeks (15 minutes, online surveys answered independently), beginning at the time of randomization as indicated in Figure 8. Parent Activation Surveys will also be administered at weeks 8 and 16 (the measure at week 8 will be used for an exploratory mediation analysis described in the analysis section 4.3.2.5). Medical records will be abstracted by RCs every four weeks. All patients  $\geq 8$  years old and parents who completed the 16-w follow-up, dropped out, and parents of children who died, and a convenient sample of providers, will be invited to participate in an Exit Interview (in-depth face-to-face or phone interview) administered by the RCs to evaluate study processes, care experience, and intervention fidelity (among those in the intervention arm). There are two points in the timeline with potential for delays. Technical issues, such as troubleshooting access to PediQUEST with participants, or other technical mishaps (which we expect to be rare events), may prolong the run-in period by one or two weeks. In addition, the scheduling of exit interviews will always occur out of the 16-week follow-up period, most frequently within the next week after the last survey is answered, but adapting to the family availability. When a patient dies within the study, the invitation for the exit interview, as explained below, is sent 12-weeks after the death. For these reasons, total enrollment time will be 18 weeks in most cases, but there will be exceptions. This will be explained during the enrollment process.

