|                                                                     | Social Support              | Medical Outcomes Study Social Support-Short Form                                                                             | 4 domains: emotional/ informational, tangible, affectionate, and positive social interaction; 8-items. High reliability ( $\alpha > 0.91$ ) and stability over time.                                                                                                                                                                                                                                                                                                                                                                                                                                                                               |
|                                                                     | Anxiety                     | Spielberger's State-Trait Anxiety Scale (S-TAI)-Trait subset                                                                 | Measures trait anxiety (20 items); evaluates relatively stable aspects such as calmness, confidence, and security. Response options: frequency of feelings "in general:" 1) almost never, 2) sometimes, 3) often, and 4) almost always. Scoring: Item scores are added. Scoring is reversed for anxiety-absent items. Range of scores for S-TAI-Trait is 20–80 (higher indicates greater anxiety). Validity and reliability are high. High stability over time.                                                                                                                                                                      |

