| Scoring range                                                                                                                                                                                                                                                                                                                          | 0-100 (100=worse)                                                                                                                |       |       | 0-100 (100=better)                                                                                                                                      |     |      |     |             |      |     | 0-100 (100=better)                                                                                           |             |

\*The collection of both parent and child data will be used only to analyse concordance. PediQUEST reports only provide feedback on child answers (or parents when children are young or do not want to answer); † PQ-MSAS 7-12 evaluates shorter time frame (past two days) and only 8 symptoms; \*Response types: L-5: 5-option Likert type; L-4: 4-option Likert type; FS-3: 3-option Faces scale; VAS: Visual analogue scale (100 mm); §Data from PQ RCT

| Monthly Parent Questionnaires (weeks 0-4-8-12-16) |                        |                                                                                   |                                                                                                                                                                                                                                                                                                                                                                                                                                                                                                                                                               |

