|                                                   | Activation             | Brief-COPE                                                           | See above. Measured at weeks 8 (for exploratory analysis see 4.3.2.5) and 16                                                                                                                                                                                                                                                                                                                                                                                                                                                                                  |

|  |  |                                          |                                                                                                                              |
|--|--|------------------------------------------|------------------------------------------------------------------------------------------------------------------------------|
|  |  | Use of complementary therapies checklist | Ad hoc checklist of complementary therapies; parents will report use (yes/no) in past four weeks and reasons for use. |
|--|--|------------------------------------------|------------------------------------------------------------------------------------------------------------------------------|

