### 3. Methods: Assignment of interventions

#### 3.1. Allocation (sequence generation, concealment, and implementation)

Participants will be randomly assigned to the intervention or control group with a 1:1 allocation as per a computer-generated randomization sequence created by study statistician, co-I [name], and stratified by center, age (2-7, 8-12,  $\geq 13$  years old), and type of cancer (hematological, non-hematological malignancies). Study personnel will not have access to the sequences. Random sequences will be embedded in REDCap by informatics personnel, ensuring best practice standards for allocation concealment. Two weeks after enrolling, at week 0, if participant meets the criteria of being a responder, i.e. having answered two or more PQ-surveys, regardless of who in the dyad answered them, the RC will be able to see study arm assignment in REDCap. The RC will begin intervention procedures by turning on the PQ-feedback report and email features of PQ web,

notifying the primary team and linking the account to the corresponding providers (primary oncologist, primary nurse, primary psychosocial clinician, and PC Response team key person) so they start to receive reports too, and letting the PC Response team administrative designated person know of the assignment so they can schedule the initial visit with the Response team (as explained in 2.3.1 and Figure 7).

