### 3.2. Blinding

After randomization, participants, PC team, oncologists, and research staff will be unblinded to group assignment, because the intervention is not amenable for blinding.

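### The protocol does not say whether the week-0 parent questionnaire is baseline or outcome for state anxiety, depression and complementary therapies, nor that it precedes arm disclosure

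*Protocol*

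**What the plan says.** Section 2.4.2.2 defines the anxiety and depression outcome as the between-arm difference in the "mean over 16-w of anxiety and depression scores measured on a monthly basis by S-TAI-State and CES-D-10". It defines two further outcomes as the total number and the number of different "complementary therapies used for symptom treatment (reported by parents every 4 weeks"), over the 16-week period.

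Table 3 gives the schedule: "Monthly Parent Questionnaires (weeks 0-4-8-12-16"). Section 2.5 says that these questionnaires go to parents in both arms, "beginning at the time of randomization as indicated in Figure 8". In Table 3, symptom-related stress (aRSQ-Stress) and Brief-COPE are limited to weeks 8 and 16 within this series. The therapy checklist is not limited, so it is also due at week 0. On it, "parents will report use (yes/no) in past four weeks and reasons for use".

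The week -2 Baseline Packet in Table 3 contains aRSQ-Stress, Brief-COPE and, for anxiety, the "Spielberger's State-Trait Anxiety Scale (S-TAI)-Trait subset". It contains no state-anxiety scale, no CES-D-10 and no therapy checklist.

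At week 0, under section 3.1, "the RC will be able to see study arm assignment in REDCap", and the coordinator then starts intervention procedures. Section 3.2 adds: "After randomization, participants, PC team, oncologists, and research staff will be unblinded to group assignment".

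The Aim 2 model (section 4.3.2.2, which refers back to 4.3.2.1) has a random effect for the subject and fixed effects for group, categorical time, group by time and the stratification factors. The only baseline score added is trait anxiety, in the state-anxiety analysis.

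**The concern.** For state anxiety, depression and therapy use, the week-0 form is the only measurement before any intervention is delivered. The protocol leaves its role open, and each possible role carries its own risk.

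- **Week 0 as an outcome point.** The 16-week mean then includes a visit at which no treatment effect is possible, which shrinks the expected difference. The therapy count then includes use that lies wholly before randomization.
- **Week 0 as baseline.** Nothing stops a parent from answering after learning the arm. Section 5.2.1 lets parents answer the monthly surveys by phone or in person, and section 2.5 has the coordinator administer phone questionnaires, so a coordinator who has already seen the arm could collect the form. Learning that one's child has been assigned to palliative care involvement could plausibly move state anxiety. Adjusting for a score already moved in this way would distort the estimated effect.

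The two risks cannot both apply to the same analysis. An analysis plan can settle which visits are averaged, but it cannot turn a form answered after disclosure into a clean baseline.

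Not affected are aRSQ-Stress and Brief-COPE, which have a study-entry measure, and psychosocial clinician encounters, which are abstracted from week 0 onward (section 2.5.2).

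**Working it through.** **Inputs (section 2.6.1 unless noted).** 68 parents per arm; one-sided alpha 0.05; d = 0.43, illustrated by a 5.2-point S-TAI-State difference with SD 12.2; stated power above 80%. Visits at weeks 0, 4, 8, 12 and 16 (Table 3).

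**1. The stated power.** With the normal approximation, power = Φ(d·√(n/2) − 1.645), and √(68/2) = 5.831.
- d = 0.43: Φ(2.507 − 1.645) = 80.6% (noncentral t: 80.2%).
- d = 5.2/12.2 = 0.426: 80.0% (noncentral t: 79.6%).

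The stated figure is reproduced.

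**2. Week 0 counted as one of five equal points.** Assume no effect at week 0 and a constant effect Δ at weeks 4 to 16. The expected difference in the five-point mean is (0 + 4Δ)/5 = 0.8Δ.
- 5.2 × 0.8 = 4.16 points; 0.43 × 0.8 = 0.344.
- If 12.2 is the SD of the mean: Φ(0.344 × 5.831 − 1.645) = Φ(0.361) = 64.1%. From 4.16/12.2 it is 63.4%.
- Regaining 80% power would take 105 per arm instead of 67.

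**3. If 12.2 is instead a single-visit SD.** The protocol does not say which it is. Under compound symmetry with correlation ρ (assumed), the mean of k visits has variance 12.2² × (1 + (k − 1)ρ)/k.

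| ρ (assumed) | Weeks 0 to 16, difference 4.16 | Weeks 4 to 16, difference 5.2 |
|---|---|---|
| 0.4 | 86.7% | 95.6% |
| 0.5 | 82.2% | 93.3% |
| 0.6 | 77.8% | 90.8% |
| 0.7 | 73.8% | 88.1% |
| 0.8 | 70.0% | 85.3% |

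In this reading, a week-0 covariate brings the power of the week 4 to 16 mean to at least 99%.

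**4. Therapy checklist.** Five forms with four-week recall span weeks −4 to 16: 5 × 4 = 20 weeks against a stated 16. The week-0 form covers weeks −4 to 0, so 4/20 = 20% of the recalled time precedes randomization.

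**5. Order of week-0 events.** Section 2.5 starts the questionnaire at randomization, section 3.1 reveals the arm at week 0, and section 3.2 says that blinding ends after randomization. No text says which comes first on that day, the form or the disclosure.

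**The case against.** A reader might infer that the protocol does average week 0 into the outcome. No text says so, and some points the other way. Section 4.3.1 separates baseline from post-baseline measurements, and week 0 is the only possible baseline for these two scales. Section 1.2.2 describes measurement every four weeks for 16 weeks, which can be read as weeks 4 to 16. The therapy count is tied to the 16-week period, which a form recalling weeks −4 to 0 falls outside. A model with categorical time and group by time can deliver a week 4 to 16 contrast, and an analysis plan may name the visits. All of this stands, so the gap is an undefined role for week 0 and not a stated error.

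A reader might also infer that parents do answer week 0 knowing the arm. That is permitted, not prescribed. Figure 8, to which section 2.5 refers for timing, is not shown and might fix the order. Three run-in surveys within two weeks suggest that some data around week 0 precede allocation, but those are the weekly surveys, not the parent questionnaire.

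Nor is the stated power shown to be wrong. Section 2.6.1 sets its effect on the mean itself; treating 5.2 points as the week 4 to 16 effect is an assumption made here. Finally, therapy use before randomization differs between arms only by chance, so counting it adds noise, not bias.

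What the objection does not remove is the missing visit definition, the missing baseline term in the model, and the missing rule on when the form is completed.

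**Conclusion.** The point holds as a gap in definition and conduct for three secondary measures: state anxiety, depression and complementary-therapy use. The protocol gives week 0 no role, its model uses no baseline value of these outcomes, and it does not protect their only pre-intervention measurement from knowledge of the arm.

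The size depends on the role chosen. Counting week 0 as an outcome point would shrink a constant effect by 20%. One-sided power would then be about 64% instead of about 80% if 12.2 is the SD of the mean, or about 70% to 87% if it is a single-visit SD with correlation 0.8 to 0.4. Equal weighting and a constant effect from week 4 are assumed throughout. If week 0 is left out of the mean, the stated power is unchanged. If week 0 is the baseline, the risk is a score influenced by allocation, and the documents give no basis for quantifying it. The primary outcome is not touched.

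**What to change.** - **Sections 2.4.2.2 and 4.3.2.2:** define week 0 as baseline and include it as a covariate. Define the anxiety and depression outcome as the mean over weeks 4, 8, 12 and 16, and use the same visits for the binary CES-D-10 analysis.
- **Therapy outcomes (2.4.2.2, 4.3.2.3):** count only the week 4 to 16 checklists, whose recall windows cover exactly weeks 0 to 16.
- **Sections 2.5 and 3.1:** release the allocation in REDCap only once the week-0 parent questionnaire is submitted or its window has closed.
- **Parents already randomized:** leave week 0 out of the mean or total. Use it as a covariate only where its timestamp precedes allocation release, state how parents without a usable week-0 score stay in the analysis, and add a sensitivity analysis without the covariate.

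The cost is a few sentences and a change in the order of two week-0 steps. No instrument or visit is added. Randomization may wait a day or two for the parent form. With the protocol already at version 17.1, the change in order helps only families not yet randomized; the definitions and the timestamp rule can still be applied to everyone.

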### 2.5.2. Medical Record Abstraction

The following variables will be abstracted from the medical records at week -2 (study entry): child diagnosis, cancer-directed treatments, and symptom treatments.

From week 0 to 16 (i.e. randomization point to end of follow-up), information will be abstracted every four weeks by RCs summarizing events that occurred in the four-week window including: disease status (stable, progression, remission), date of change in status when appropriate, cancer-directed and symptom treatments, formal PC referrals, hospitalizations, No. of psychosocial clinician encounters and No. of PC encounters documented. Chart abstraction forms will be entered into PediQUEST web.

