## 2.6. Sample Size

The target sample size (SS) is N=136 participants 68 in each arm. Texas Children's Hospital will have a slightly lower accrual goal of 34 total dyads, as opposed to 50 dyads, since they will collect data for a shorter period of time. Based on prior work, we estimate that there will be approximately 32 eligible patients/site/year, representing a total of 288 eligible patients over the 36 months the study will be available for recruitment. Pilot data suggest an enrollment rate of 70% which translates into approximately 200 patient-parent dyads, our enrollment target. After the two-week run-in period, non-responders will be excluded. Assuming that about 25% will be non-responders, a conservative estimate based on pilot data, there would remain 150 patients to be randomized to either the intervention (n=75) or usual cancer care (control, n=75). Based on previous work we estimate an attrition of approximately 10%, mainly due to dropouts. We therefore expect to collect complete data on a minimum of 136 dyads, 68 per group, a sample size that achieves sufficient power for all outcomes.

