### 4.3.2. Analysis Plan

#### 4.3.2.1. Comparison of patient-level outcomes (HRQoL and Symptom distress) - Specific Aim 1

The effect of the intervention on child quality of life and symptom burden outcomes (see section 2.4) will be estimated using mixed linear models, with patient as a random effect and group, time (categorical) and group x time interaction and the stratification factors as fixed effects. . The same analysis will be undertaken for the respective domain subscales of PedsQL (physical and psychosocial) and PQ-MSAS (physical and psychological).

#### 4.3.2.2. Comparison of parent-level outcomes (anxiety, depression, HRQoL, and burden) - Specific Aim 2

The same analytical approach described for patient-level outcomes will be followed to analyze parent S-TAI-State, CES-D-10 mean scores and aRSQ symptom-related scores. In S-TAI-State analysis, we will additionally adjust by baseline S-TAI-Trait score. We will also compare depression (CES-D-10  $\geq 10$ ) over time between the two groups using generalized linear mixed models with logit link and binomial distribution. As gender is a predictor of these outcomes, it will be included in these models if imbalanced between arms.

#### 4.3.2.3. Comparison of family activation outcomes - Specific Aim 3

Mixed models, similar to those described for patient-level outcomes, will be fitted to estimate the effect of the intervention on change between week 16 and baseline in Brief COPE active coping, planning, and instrumental support Scores, Total No. of, and No. of different, complementary therapies, and No. of psychosocial clinician encounters over the 16-w study period. Link and distribution for these models will be defined based on the distribution of the outcome variable. We will explore whether change in parent's activation score is modified by parent/child characteristics (e.g. parent's gender, S-TAI-Trait, CES-D-10 scores; and child's diagnosis, among others) including the corresponding interaction terms.

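### Complementary-therapy use and psychosocial encounters are defined as 16-week totals with no denominator for time observed, so unequal retention could bias the secondary Aim 3 comparison

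*Protocol*

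**What the plan says.** Section 2.4.2.2 lists four family-activation outcomes. One is a change in coping scores. The others are counts: two for complementary therapies, "b) Total No. and (c) No. of different complementary therapies used for symptom treatment (reported by parents every 4 weeks"), and one for psychosocial services, "as measured by total No. of psychosocial clinician encounters documented in the medical record, over the 16-w study period". Section 4.3.2.3 repeats the counts as "Total No. of, and No. of different, complementary therapies, and No. of psychosocial clinician encounters over the 16-w study period".

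The two kinds of count have different sources. Therapies come from a monthly parent checklist (Table 3), on which "parents will report use (yes/no) in past four weeks and reasons for use". Encounters come from the chart: under section 2.5.2, from week 0 to week 16, "information will be abstracted every four weeks by RCs summarizing events that occurred in the four-week window".

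On the analysis, section 4.3.2.3 says "Mixed models, similar to those described for patient-level outcomes, will be fitted to estimate the effect of the intervention", with link and distribution to be chosen from the data. Section 4.3.3 gives general options for missing data: complete-case analysis, multiple imputation, inverse probability weighting and sensitivity analyses, depending on the missingness mechanism.

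Three further provisions bear on who is only partly observed. Section 2.3.2 removes a dyad when the parent or the child misses four consecutive PediQUEST surveys, with rare exceptions. Section 2.6 states "we estimate an attrition of approximately 10%, mainly due to dropouts". Section 4.3.1 analyses every randomised participant with baseline and at least one post-baseline measurement.

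**The concern.** A total depends on how long, and how completely, a family was observed. In the same section 2.4.2.2, anxiety and depression are means over 16 weeks, which a missed assessment does not mechanically lower. A total is lowered unless something corrects it.

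The protocol makes partial observation likely. A child's missed weekly surveys can end the parent's therapy reporting, and a family with one answered window can be analysed beside a family with four. Retention could differ by arm, because the trial is unblinded and only the intervention arm receives reports and Response-team contact. The direction is unknown. Better retention in the intervention arm would look like support for H3, and worse retention would hide a real effect.

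The two endpoints are exposed in different ways. Skipped questionnaires affect therapies only. Encounters are cut short by death, and by removal or dropout only if abstraction then stops, which the protocol leaves unsaid.

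**Working it through.** **1. The plan's own figures.** Inputs from section 2.6.1: 68 per arm, one-sided α = 0.05; encounters, difference 2 and SD 4.5, stated power 82%; therapies, effect size 0.43, stated power 80%.

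Power = Φ(difference / (SD × √(2/n)) − 1.645).

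- Encounters: SE = 4.5 × √(2/68) = 0.772; Φ(2/0.772 − 1.645) = 82.8%.
- Therapies: Φ(0.43/0.1715 − 1.645) = 80.6%.

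Both reproduce. They take one complete total or mean per family.

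**2. How a summed total depends on windows.** Monthly questionnaires at weeks 4, 8, 12 and 16 give four post-randomisation windows. A parent using three therapies throughout scores 3 × 4 = 12 with four answered and 3 × 2 = 6 with two. The use is the same and the score is halved.

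**3. Encounters, illustration.** Assumptions not in the documents: no true effect, unobserved time adds nothing to the total, and a mean complete total M of 4 to 8. Let g be the arm gap in the share of follow-up observed.

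False difference = M × g; one-sided false-positive rate = Φ(M × g / 0.772 − 1.645).

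| g | False difference (M = 4 to 8) | Share of planned 2 | False-positive rate |
|---|---|---|---|
| 5 points | 0.2 to 0.4 | 10% to 20% | 8% to 13% |
| 10 points | 0.4 to 0.8 | 20% to 40% | 13% to 27% |
| 20 points | 0.8 to 1.6 | 40% to 80% | 27% to 67% |

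To scale g against the expected attrition of about 10%, assume that those who leave do so at mid-follow-up. Dropout of 15% v 5% then gives g = (0.15 − 0.05) × 0.5 = 5 points, and 20% v 0% gives 10 points. The 20-point row lies beyond what the protocol expects.

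**4. Equal loss in both arms.** No false difference arises, but a true difference of 2 shrinks. Losing 5% of follow-up leaves 1.9 (power 79%), 10% leaves 1.8 (75%) and 20% leaves 1.6 (67%).

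**5. Therapies, illustration.** The documents give no mean or SD in therapy counts. Assumptions: mean 3 per window in both arms, between-family coefficient of variation about 0.7, four windows answered independently of use, unanswered windows adding nothing, 68 per arm, 4,000 simulated trials per row, one-sided 5% test.

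| Answered, control v intervention | False positives, totals | False positives, per answered window |
|---|---|---|
| 75% v 75% | 5% | 5% |
| 75% v 80% | 11% | 5% |
| 70% v 80% | about 21% | 5% |
| 65% v 85% | 54% | 4% to 5% |

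The 70% v 80% row has an expected spurious difference of 4 × 3 × 0.10 = 1.2 therapies, about 0.15 SD, or roughly a third of the 0.43 used for power (0.15/0.43 = 35%).

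**The case against.** The strongest reply is that the protocol nowhere counts an unanswered window as zero. The model is described as similar to the patient-level one, which has a patient random effect and categorical time. Fitted to four-weekly records, it would treat a skipped window as missing. Section 2.6.1 speaks of the mean number of therapies, section 1.2.3 of reporting every four weeks, and section 4.3.3 offers imputation or weighting and promises robustness checks in all cases. Counting rules may also stand in an SAP that is not shown. All of this is fair, and it means that bias cannot be asserted as built into the plan. But the outcome named in 2.4.2.2 and 4.3.2.3 is still the 16-week total. The model wording permits a per-window analysis without requiring it. Section 4.3.3 does not say whether a partial total is a missing value or a valid low one, and imputation or weighting comes into play only in the first case.

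Four stronger readings are tempting and are not supported:

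- A reader might infer that skipped questionnaires lower the encounter count. They cannot, because encounters come from charts.
- A reader might infer that the yes/no checklist forces summing, since total and different therapies would otherwise coincide within a window. Reasons for use are also recorded, so a therapy used for two symptoms could be counted twice in one window. Summing across windows is the natural reading, not the only one.
- A reader might take the pilot response figures in section 2.3.3 ("over 75% of participants answered 50% of weekly surveys or more, and 60% answered 75% of weekly surveys or more") as the expected questionnaire response. They concern weekly surveys. That section's remark on controls' incentive to report explains why as-needed reporting was rejected, and is not evidence about this schedule.
- A reader might call a low count after death false. As a count it is true. Whether to count per day alive is a choice of estimand, which the protocol should state.

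The run-in, and the reminders, gift cards and coordinator follow-up provided in both arms, should also limit the gap in response.

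**Conclusion.** The point holds as a conditional one. Two therapy counts and one encounter count are fixed as 16-week totals without a denominator, while the removal rule and the analysis set admit partly observed families. If the totals are summed as worded, differential retention biases the Aim 3 contrast in either direction, and equal loss dilutes it.

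The size cannot be derived from the documents. The figures above rest on assumed means, assumed response gaps and missing time adding nothing to the count. They show what could happen and do not estimate this trial's error rate. Nor is every arm difference in response damaging: a small gap gives a small bias. At 15% v 5% dropout, under the mid-follow-up assumption, the false difference is 0.2 to 0.4 encounters against the planned 2.

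These are secondary outcomes, and the primary PedsQL comparison is unaffected. The change is still worth making because it costs little, and whether charts of removed dyads are abstracted has to be settled while the trial is running.

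**What to change.** 1. **Therapies (2.4.2.2, 4.3.2.3).** Analyse the number of therapies per answered four-week window (weeks 4, 8, 12, 16) in a count mixed model, with one record per answered window and a family random effect. Alternatively, keep the total with an offset of log(windows answered). Treat the cumulative number of different therapies as descriptive, because it does not scale simply with windows answered.
2. **Encounters (2.4.2.2, 4.3.2.3).** Model the count with an offset of log(days observed from randomisation), and state how death before week 16 is handled.
3. **Abstraction (2.5.2).** State that four-weekly chart abstraction continues to week 16 or death for every randomised child, including those in dyads removed for missed surveys, unless permission to use records is withdrawn.

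The cost is a few sentences. Therapy data are already collected by window, and abstraction asks nothing of families. The endpoint will read as a rate rather than a simple total, and there is slight extra abstraction for removed dyads.
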